# Effects of Qingda granule on patients with grade 1 hypertension at low-medium risk: study protocol for a randomized, controlled, double-blind clinical trial

**DOI:** 10.1186/s13063-022-07006-0

**Published:** 2023-01-02

**Keywords:** Hypertension, Qingda granule, Blood pressure, Randomized controlled trials

## Abstract

**Background:**

Numerous pre-clinical studies showed that Qingda granule (QDG) was effective in treating hypertension. This study aims to evaluate the efficacy and safety of QDG in reducing blood pressure among patients with grade 1 hypertension at low-medium risk.

**Methods:**

The study is designed as a randomized, multi-center, double-blinded, non-inferiority clinical trial. Five hundred fifty-two patients with grade 1 hypertension at low-medium risk from 13 hospitals will be recruited and randomly assigned to the QDG group (*n* = 276, treated with valsartan capsule simulation agent and QDG) or control group (*n* = 276, treated with valsartan capsule and QDG simulation agent). The treatment period will be 4 weeks and the follow-up period will last 4 weeks after treatment. Primary outcome will be a decreased value of systolic blood pressure and diastolic blood pressure after treatment. And second outcome will include the decreased value of diastolic blood pressure and systolic blood pressure at the end of follow-up, the percentage of participants achieving normal blood pressure at the end of treatment and follow-up, the Hamilton Anxiety Scale and TCM syndrome scores at the end of treatment and follow-up, and levels of hypertensive hormones at end of treatment and follow-up.

**Discussion:**

This study will provide initial evidence regarding the clinical efficacy and safety of QDG in treating grade 1 hypertension at low-medium risk.

**Trial registration:**

Chinese Clinical Trial Registry ChiCTR2000033890. Registered on 15 June 2020.

**Supplementary Information:**

The online version contains supplementary material available at 10.1186/s13063-022-07006-0.

## Background

About 1.13 billion individuals suffer from hypertension around the world, with fewer than 20% of them being controlled to normal blood pressure [1]. Previous studies demonstrated that hypertension could increase the risk of coronary heart disease, stroke, and end-stage renal disease [2–4]. Although antihypertensive drugs are effective in treating hypertension and decreasing hypertension-associated risks, the side effects of these drugs often result in the discontinuation of the prescription [5, 6].

Traditional Chinese medicine (TCM) has shown efficacy in treating hypertension without severe side effects [7]. In particular, *Qingxuan Jiangya* decoction (QXJYD) has been used for the treatment of hypertension for many years in clinical practice [8]. QXJYD can decrease blood pressure and arterial vascular remodeling in spontaneously hypertensive rats [8, 9].

*Qingda* granule (QDG) formulation, simplified from QXJYD. The main drug components include *Gastrodia elata*, *Uncaria*, *Scutellaria baicalensis*, and lotus germ, which were shown to attenuate elevated blood pressure and promote vasorelaxation of thoracic aortic rings in the animal study with spontaneously hypertensive rats [10]. Some QDG components such as rhynchophylline, gastrodin, and baicalin have antihypertensive effects [9, 11, 12]. These findings have provided important evidence to further validate the anti-hypertensive effects of QDG in clinical trials. In the currently multi-center, double-blinded, randomized controlled non-inferiority trial, the objective is to evaluate the effects and safety of QDG compared with valsartan.

## Design and method

### Study setting

The study is a randomized, multi-center, double-blinded, non-inferiority clinical trial. The protocol for the trial was approved by the Medical Ethics Committee of Xiyuan Hospital of the Chinese Academy of Chinese Medical Sciences (2020XLA027-3) and registered in the Chinese Clinical Trial Registry (http://www.chictr.org.cn/showproj.aspx?proj=55279) with number ChiCTR2000033890 on 15 June 2020. The protocol is written in accordance with the Standard Protocol Items: Recommendations for Interventional Trials (SPIRIT), showed as Supplementary File 1 [13]. And the schedule of enrolment, interventions, and assessments is shown in Fig. 1 and the study flowchart is shown in Fig. 2.

**Fig. 1 Fig1:**
[figure not shown]
SPIRIT schedule of enrolment, interventions, and assessments. Abbreviations: MACCEs, major adverse cardiac and cerebrovascular events; TCM, traditional Chinese medicine

**Fig. 2 Fig2:**
[figure not shown]
Study flow chart

### Participants

Inpatients and outpatients diagnosed with grade 1 hypertension (at low-medium risk) from 13 hospitals (Supplementary File 2) will be screened based on the inclusion and exclusion criteria. The researchers will recruit inpatients and outpatients and gain the informed consent from the patients during the admission to the outpatients or to the hospital.

### Inclusion criteria

Grade 1 hypertension (low-medium risk) is diagnosed according to the Chinese Guidelines for the Prevention and Treatment of Hypertension [14].The participants do not take any antihypertensive medicine within 1 month of starting the trial.The age of the participants ranges from 20 to 75 years (inclusive).Participants are informed about the trial and voluntarily sign a consent form.

### Exclusion criteria

Participants with obvious liver or kidney diseases, alanine transaminase (normal value: 0–40U/L) and aspartate transaminase values (normal value: 29–35U/L) 1.5 times higher than the upper reference limit, or blood creatinine and urea nitrogen levels higher than the upper reference limit.Participants with serious mental illness, hematopoietic disease, malignant tumor, or other major diseases.Women currently pregnant or preparing for pregnancy.Involvement in other clinical trials within 3 months before enrollment.Suspected or definite allergy to the ingredients of the study drug.

### Withdrawal, dropout, and discontinuation

Enrolled participants that fail to complete all the assessments of the trial, regardless of when or why, will be considered to have withdrawn. Reasons for withdrawal will be recorded on case report forms (CRFs), and data for these participants will be included in the final analysis only up to the last follow-up.

The trial can be terminated in the following cases: (1) participant(s) develop grade II or III hypertension, and other antihypertensive medicines should be added based on treatment guidelines [15], (2) no effects of the test drugs are observed during the trial, or a decision to terminate is taken (3) based on financial or management reasons or (4) by administrative authorities.

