### Intervention

The course of treatment will last 4 weeks, and patients will be followed up for 4 additional weeks to assess any persistent effects of the drug. Participants will be examined at week 0 (baseline, visit 2), week 4 (end of treatment, visit 3), and week 8 (end of follow-up, visit 4). The QDG group will be treated with valsartan capsule simulation agent (80 mg, once daily for 4 weeks) and QDG (5 g, twice daily for 4 weeks), while the control group will be treated with valsartan capsule simulation agent (80 mg, once daily for 4 weeks) and QDG simulation agent (5 g, twice daily for 4 weeks). The drugs and simulation agents will be provided by Jiangyin Tianjiang Pharmaceutical (Jiang’yin City, China). The simulation agent will be prepared using soluble starch, colorant, and a bitter additive to achieve appearance, smell, and taste comparable to the drug. The drugs and simulation agents will be identical in outer packaging, color, shape, and flavor. The drug that patients did not take would be returned to the researcher. And no other anti-hypertension drugs should be taken during the study process.

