### Safety

At visits 2–4, safety data will be collected based on vital signs (respiratory, heart rate, and body temperature) and electrocardiography (ECG). We will request consent for the collection of blood and urine samples to assess hepatic and renal function. The blood and urine samples will be collected at 13 hospitals and stored at room temperature. After completion of sample collection, laboratory analysis will be conducted in the laboratories of hospital. The remaining samples will be destroyed after being examined. Adverse events (AEs), defined as negative or unintended clinical manifestations following treatment, will be observed and recorded throughout the trial. If an AE occurs, the clinical researcher will adopt appropriate measures to guarantee the safety of participants. If a serious AE occurs, the clinical researcher will report it to the Medical Ethics Committee and a decision will be taken whether to terminate the trial. When the patients develop to grade II or III hypertension, adverse events (AEs) will be reported to the data monitoring committee as well as the medical ethics committee. The severity and causality will be estimated by researchers.

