### Statistical analysis

The data analysis will be based on the principle of intention to treat (ITT), and potential missing values will be filled in using data from the last observation. Data will be presented as mean ± standard deviation, median with range, or number and percentage. Data will be analyzed using SAS 9.3 software (SAS Institute, Cary, NC, USA) using two-sided tests and a significance level of *p* < 0.025. For comparison between groups, two independent sample *T*-test (group *T*-test ) and Wilcoxon rank sum test were used for measurement data. The Pearson chi-square test or Fisher exact test was used for counting data. Wilcoxon rank sum tests were used for grade data. For intra-group comparison, paired *T*-tests or Wilcoxon symbolic rank test was used for measurement data. CMH chi-square tests were used when considering the central effect. Sub-group analyses will be conducted based on the characteristics of included participants.

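### The rule for progression to grade II or III hypertension is worded as a ground for ending the whole trial, and its call for added antihypertensives conflicts with the unqualified ban in the Intervention section

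*Protocol article*

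**What the plan says.** The Withdrawal, dropout, and discontinuation section opens its second paragraph with "The trial can be terminated in the following cases: (1) participant(s) develop grade II or III hypertension, and other antihypertensive medicines should be added". The other items in that list are lack of effect of the test drugs, financial or management reasons, and a decision by the authorities. The same section counts as withdrawn only those who do not complete every assessment.

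The Intervention section states "And no other anti-hypertension drugs should be taken during the study process" and makes no exception for progression. It schedules examinations at weeks 0, 4 and 8 (visits 2, 3 and 4).

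The Safety section adds a reporting rule: "When the patients develop to grade II or III hypertension, adverse events (AEs) will be reported to the data monitoring committee", and also to the ethics committee. For serious adverse events it says that "a decision will be taken whether to terminate the trial".

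The Statistical analysis section adopts intention to treat, with gaps filled by the last observation. The article does not say how pressures measured after an added antihypertensive are to be treated.

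**The concern.** Two things are wrong in the printed text.

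First, the level of the rule. One participant's progression is listed as a case for ending the study as a whole. A criterion that is nearly certain to be met cannot tell a trial that should stop from one that should not.

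Second, the sections disagree on added drugs. One says that they should be given on progression; the other says that none may be taken. Thirteen hospitals could resolve this in different ways. The status of a participant who is given another drug and still attends every visit is left open.

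In a non-inferiority trial the direction matters. If other antihypertensives are used more often in the weaker arm, they lower that arm's pressure, shrink the difference, and make non-inferiority easier to declare.

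**Working it through.** The protocol gives no figure on this point to reproduce, and no progression or added-drug rates. Steps 2 and 4 therefore rest on assumptions.

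**1. The sections side by side.** Under Withdrawal, a participant who progresses should have other antihypertensives added. Under Intervention, no participant takes any during the study. Both hold only if every such participant leaves the study, and no section says so. The Safety and Interim analysis sections speak of terminating the trial only in the sense of the whole study, so the same phrase under Withdrawal naturally carries that sense.

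**2. How likely is the literal trigger?**
- From the Sample size section: systolic falls of 12.0 ± 10.5 (QDG) and 12.9 ± 11.8 (valsartan) mm Hg. N = 552.
- Assumed: grade II begins at 160 mm Hg systolic; a common baseline of 145, 150 or 155 mm Hg; normality; diastolic pressure ignored.
- Formula: p = 1 − Φ((160 − (baseline − fall)) / SD).

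| Baseline | QDG | Control |
|---|---|---|
| 145 | 1 − Φ(27.0/10.5) = 0.51% | 1 − Φ(27.9/11.8) = 0.90% |
| 150 | 1 − Φ(22.0/10.5) = 1.8% | 1 − Φ(22.9/11.8) = 2.6% |
| 155 | 1 − Φ(17.0/10.5) = 5.3% | 1 − Φ(17.9/11.8) = 6.5% |

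Applied to 552 participants, these rates give about 3 to 36 cases (552 × 0.0051 = 2.8; 552 × 0.0646 = 35.7). The chance of at least one is 1 − (1 − p)^552, which is 94% at the lowest rate and above 99.9% at baselines of 150 and 155. At a rate of only 0.1% it would be 42%.

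**3. When would pressures on added drugs enter the comparison?**
- Drugs added before visit 3, participant stays: visit 3 (primary) and visit 4 are both measured on added drugs.
- Progression first found at visit 3: the primary measurement has already been taken, so only visit 4 (week 8, secondary) is affected. No examination is scheduled between weeks 0 and 4, so this is the likelier route.
- Participant leaves before visit 3: the last observation is most likely baseline, so the change is scored as zero and no pressure on added drugs enters.

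In the first two cases the participant completes all assessments, is not withdrawn, and remains in the intention-to-treat analysis.

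**4. Size under the same model.** Put QDG exactly at the margin: a fall of 12.9 − 3 = 9.9 mm Hg. The QDG rates become 0.89%, 2.9% and 7.8%, against 0.90%, 2.6% and 6.5% in control. The excess in QDG is about 0, 0.3 and 1.3 percentage points. Assume that added drugs lower systolic pressure by a further 5 to 10 mm Hg:
- Shift = excess × drug effect, at most 0.0133 × 10 = 0.13 mm Hg.
- SE = √((11.8² + 10.5²)/276) = √(249.49/276) = 0.951.
- False non-inferiority rate, taking 2.5% one-sided as nominal, = Φ(shift/0.951 − 1.96), which is 2.5% at no shift and Φ(0.14 − 1.96) = 3.4% at 0.13 mm Hg.

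For the primary outcome this is an overstatement, because it treats everyone at or above 160 at week 4 as if already on added drugs when measured.

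**The case against.** The strongest reply is that the rule was meant for individuals. It stands under a heading about withdrawal and discontinuation, and it says that the trial can be terminated, not that it will be. If participants who need other drugs simply leave, the conflict with the Intervention section largely disappears. That reading is plausible, but it is not printed: the other grounds in the list concern the whole trial, and no section says that these participants leave. The permissive wording does stand, and it means that no automatic stop is prescribed.

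A reader might also infer that three sections are mutually incompatible. They are not. The Safety text is a reporting rule that fits either reading, and the firm conflict is between Withdrawal and Intervention.

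It can fairly be said that the analysis of pressures after added drugs may be set out in an analysis plan or full protocol that is not shown. Its absence from the article is therefore not the point. The point is the contradiction in what is printed, and its consequence if nothing else governs.

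Finally, under the planned effects the model gives fewer progressors on QDG than on control (for example 5.3% against 6.5%). Any resulting bias would then run against non-inferiority. This stands, and it shows that the direction cannot be taken for granted.

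**Conclusion.** The point holds as a conflict between two sections and as a criterion set at the wrong level. Under the assumed cut-off and baselines, the literal criterion is 94% to over 99.9% likely to be met, so it gives no guidance on when to stop.

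The consequence for the analysis is conditional. Pressures on added drugs enter mainly the week 8 secondary comparison, and reach the week 4 primary only for participants whose drugs were added before visit 3 and who stayed. The size is unknown. The model at the margin gives about 0 to 0.13 mm Hg and a one-sided error of about 2.5% to 3.4%.

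A reader might infer serious inflation. If 10% of QDG and 3% to 5% of control participants took added drugs worth 5 to 10 mm Hg, the shift would be (0.10 − 0.05) × 5 = 0.25 to (0.10 − 0.03) × 10 = 0.70 mm Hg, and the error about 4.5% to 11%. Nothing in the protocol supports such a split, and the model built on its own planned falls does not produce it. The bias would be large only if added drugs were much more frequent in the QDG arm.

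**What to change.** Reconcile the Withdrawal and Intervention sections so that their position on other antihypertensives agrees. List participant-level discontinuation separately from trial-level termination. Which clinical rule applies is for the investigators to decide.

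The Trial status section says that recruitment has ended and the data are being analysed, so new data collection is not a realistic remedy. From data already recorded, report by arm how many participants progressed and how many received another antihypertensive, before and after visit 3. Add one sensitivity analysis, at week 4 and week 8, that does not credit pressures taken after such a drug to the randomised treatment.

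The cost is a wording clarification, a short table and one extra analysis. The downside is a possibly slightly less favourable non-inferiority result.

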### Sample size

The target sample size was calculated according to the decreased value of systolic blood pressure (12.9±11.8 mm Hg) observed after 8-week treatment with valsartan capsules in a randomized clinical trial [16], and the non-inferiority margin of QDG has been established as −3 mm Hg. The decreased value of QDG on systolic blood pressure was 12.0±10.5 mm Hg, which was calculated based on our clinical practice. The minimal sample size to achieve a type I error rate of *α* = 0.05 and a power of 80% (type II error rate *β* = 0.2) is 440 participants. The size was calculated using the formula:$$n=\frac{{\left({Z}_{1-\alpha }+{Z}_{1-\beta}\right)}^2\times \left({\upsigma}_1^2+{\upsigma}_2^2\right)}{{\left(\varepsilon -\delta \right)}^2}$$where σ_1_ and σ_2_ are the standard deviations of the QDG and control groups, respectively; *ε* is the mean difference between the two groups; δ is the non-inferiority margin; *α* is the type I error rate; and *β* is the type II error rate. The study will strive to enroll 550 participants to compensate for a dropout rate as high as 20%. For convenience of randomization, we will aim to recruit 552 patients.

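### The stated minimum of 440 participants for 80% power does not follow from the protocol's own formula and inputs, which give 350 per group (700 in total); at the stated alpha, power is about 63% with 440 analysed and nominally 71% with all 552

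*Protocol article*

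**What the plan says.** All of the relevant figures are in the Sample size section of the protocol article, apart from the analysis level.

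- Control arm: the "decreased value of systolic blood pressure (12.9±11.8 mm Hg) observed after 8-week treatment with valsartan capsules".
- QDG arm: "The decreased value of QDG on systolic blood pressure was 12.0±10.5 mm Hg", attributed to the team's clinical practice.
- Margin: "the non-inferiority margin of QDG has been established as −3 mm Hg".
- Error rates and result: "The minimal sample size to achieve a type I error rate of *α* = 0.05" together with "a power of 80% (type II error rate *β* = 0.2) is 440 participants".
- Formula: n = (Z(1−α) + Z(1−β))² × (σ1² + σ2²) / (ε − δ)², where ε is defined as the between-group difference in means and δ as the margin.
- Dropout: "The study will strive to enroll 550 participants to compensate for a dropout rate as high as 20" per cent, then rounded up to 552 for randomisation. The Abstract gives 276 per group.

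The Statistical analysis section sets a different level, "using two-sided tests and a significance level of *p* < 0.025". It also specifies intention to treat, with missing values filled from the last observation.

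**The concern.** The section gives a formula, all of its inputs and a result, so a reader can repeat the calculation, and the result does not come out. The gap is too large for rounding or a small-sample correction.

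The 80% power claim for the non-inferiority comparison on systolic blood pressure rests on this figure. If the design is less powerful than stated, a failure to show non-inferiority is weaker evidence against QDG than an 80% claim suggests. The size and power statements would also be carried into the results paper uncorrected.

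**Working it through.** **Inputs (Sample size section).** σ1 = 10.5 and σ2 = 11.8, so σ1² + σ2² = 110.25 + 139.24 = 249.49. ε = 12.0 − 12.9 = −0.9. δ = −3. ε − δ = 2.1, and its square is 4.41. Z(0.95) = 1.645 and Z(0.80) = 0.842, so the squared sum is 6.1826 (from unrounded quantiles).

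**What reproduces.** 440 / (1 − 0.20) = 550, rounded to 552, which is 276 per group. This fixes 440 as a total of 220 per group.

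**What does not.** With n in each arm, the difference in means has variance (σ1² + σ2²)/n, so the printed formula gives the size per group:

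n = 6.1826 × 249.49 / 4.41 = 349.8, so 350 per group and 700 in total (700 / 0.8 = 875 with 20% dropout).

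440 / 700 = 0.63, so the stated figure is 37% too low. A t-based calculation gives 351 per group, which does not close the gap.

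**Other readings tried.**

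| ε | One-sided alpha | n per group | Total |
|---|---|---|---|
| −0.9 | 0.05 (as stated) | 350 | 700 |
| −0.9 | 0.025 | 445 (444.04 before rounding) | 890 |
| −0.9 | 0.0125 | 538 | 1076 |
| 0 | 0.05 | 172 | 344 |
| 0 | 0.025 | 218 (217.58 before rounding) | 436 |
| +0.9 (sign reversed) | 0.05 | 102 | 204 |
| +0.9 (sign reversed) | 0.025 | 129 | 258 |

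Using one standard deviation for both arms at the stated ε and alpha gives 310 (SD 10.5) or 391 (SD 11.8) per group. Two rows come close to 440. One is the total of 436 from a zero difference with Z(0.975), for which 440 would have 80.4% power. The other is the 445 per group at one-sided 0.025, if a per-group number were taken as the total. Both depart from what the section states, and neither equals 440.

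**Power under the stated assumptions.** Power = Φ(2.1 / SE − Z(1−α)), with SE = √(249.49 / n).

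- 220 per group: SE = 1.065 and 2.1 / SE = 1.972. At alpha 0.05: Φ(1.972 − 1.645) = Φ(0.327) = 62.8%.
- 276 per group: SE = 0.951 and 2.1 / SE = 2.209. At alpha 0.05: Φ(2.209 − 1.645) = Φ(0.564) = 71.4%.

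| One-sided alpha | 440 analysed | 552 analysed |
|---|---|---|
| 0.05 (Sample size section) | 62.8% | 71.4% |
| 0.025 (stated in neither section) | 50.5% | 59.8% |
| 0.0125 (two-sided 0.025, read literally) | 39.4% | 48.7% |

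The 552 column is nominal. According to the Intervention section, the week-4 visit is the first examination after baseline. For a participant without it, carrying the last observation forward may simply insert the baseline value.

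**The case against.** A reader might go further and infer that the trial has only 50–63% power, or roughly an even chance of success. The documents do not support that as the headline. The range assumes that exactly 440 are analysed, whereas the Statistical analysis section plans intention to treat with filled values, which could bring in all 552. Its lower end uses one-sided 0.025, a level that neither section states: the Sample size section has 0.05 in a one-sided quantile, and the analysis section has two-sided 0.025, literally one-sided 0.0125. One-sided 0.025 may be what was meant, but that is inference. At the alpha used for the sample size, the range is 63% to 71%.

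It is also tempting to name the slip behind 440. The two near matches are conjecture, and the sponsor should say what was done.

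It can fairly be said that recruitment is over, that a planning error neither biases the estimate nor inflates the type I error, and that a confidence interval set against the margin will show any imprecision directly. All of this stands and limits the consequence. It does not make the printed result right.

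A separate analysis plan or the full protocol might settle the analysis alpha. Neither could make 440 follow from the inputs printed here, and a stricter alpha widens the gap.

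**Conclusion.** The concern holds as an arithmetic error in the Sample size section. The printed formula and inputs require 350 per group, 700 in total, against a stated 440. At the section's own alpha, the design has about 63% power with 440 analysed and nominally about 71% with 552, not 80%. No combination examined with the stated difference of −0.9 mm Hg reaches 80% at 440 or 552.

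These figures rest on the protocol's planning values for systolic pressure, a normal approximation and 1:1 allocation. The results at one-sided 0.025 and 0.0125 are sensitivity figures until the two alpha statements are reconciled.

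**What to change.** Make a disclosed correction to the Sample size section:

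1. Keep all stated inputs on record, including the 12.0 and 12.9 mm Hg decreases. With the trial already in data analysis (Trial status section), deleting a planning assumption would rewrite the record to fit the number.
2. State that the printed formula and inputs give 350 per group, 700 in total, at one-sided alpha 0.05.
3. Disclose the alpha and ε that actually produced 440. If it was a zero difference with Z(0.975), which gives 436 in total, say so.
4. Reconcile the alpha in the Sample size and Statistical analysis sections, stating whether it is one-sided or two-sided.
5. Restate the power of 440 evaluable and 552 randomised at that reconciled alpha, taking the matching row of the power table above if it is one of those three levels. Mark the 552 figure as nominal.

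The cost is wording only, and the stated power becomes less favourable. No extra enrolment is needed.
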